### Recruitment {15}

A total of five contributing centers are planned to participate, who aim to include an average of 27 patients per year. The recruitment of all 268 patients should be completed within 24 months.

### Assignment of interventions: allocation

#### Sequence generation {16a}

The patient identification number will consist of four digits (one digit for the contributing center and three digits for the consecutive patient number). After registration, patients will be randomized in a 1:1 ratio to receive either standard skin care supported by a reminder app (Arm A) or standard skin care (Arm B) for treatment of radiation related skin toxicity. Allocation of a patient to a treatment arm will be performed in the form of a stratified block-randomization with random block size using an electronic case report form (eCRF).

Stratification will be done using the following prognostic factors:1.Treatment volume: Breast or chest wall alone vs. breast or chest wall plus lymph nodes2.Radiation boost: Yes vs. no3.At least one risk factor of dermatitis: Yes vs. no (Risk factors include chronic inflammatory disease, significant cardiovascular disease, and smoking history of >10 pack years.)

The corresponding document will be kept at the institution which performs the randomization until the end of the study. Afterwards, the original randomization list will be kept in the trial master file at the trial center of the coordinating investigator for a minimum of 10 years after the final report. The randomization will be performed via eCRF centrally by an external company using its standard software. The randomization process is based on this company’s standard operating procedures (SOPs). Once the randomization is allocated to the patient it cannot be changed.

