## Methods: Participants, interventions and outcomes

### Study setting {9}

The study will be performed in Germany (one university hospital, two academic teaching hospitals, one private practice) and Denmark (one university hospital). Participating sites can be seen at clinicaltrials.gov.

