### Intervention description {11a}

#### Standard skin care

In both the experimental arm (A) and the control arm (B) standard skin care has to be performed by the patient from the start of radiotherapy. The patients are supposed to perform the skin care four times a day. Standard skin care may vary at the participating centers. At the University of Lübeck, it includes fatty cream with 2-10% urea (fatty cream alone, if patients do not tolerate urea) and, in case of pruritus, addition of mometasone furoate cream.

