### Sample size {14}

The null hypothesis of equal rates of grade ≥2 skin toxicity is tested against the two-sided alternative hypothesis of different rates. Based on this hypothesis system, the sample size required for this trial is calculated considering the following assumptions:● A Chi-square Test will be applied● The two-sided significance level is set to 5%● In patients treated with hypo-fractionated radiotherapy for breast cancer, a retrospective pre-study suggested a rate of grade ≥2 dermatitis of 25.4% if standard skin care alone was administered [12].● Based on these retrospective data, a rate of grade ≥2 skin toxicity of approximately 30% was assumed in the reference group of a prospective trial, i.e. in patients receiving standard skin care alone for radiation dermatitis.● The impact of the Reminder App will be considered to be clinically relevant, if the rate of grade ≥2 dermatitis can be reduced to 15%.● The power to yield statistical significance if the difference in rates is in fact 15% is set to 80%.

Based on these assumptions, 131 patients are required per study arm within the Full Analysis Set. Considering that 2% of patients will not qualify for this set, a total of 268 patients should be randomized.

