In a previous retrospective study of our group that included 327 breast cancer patients irradiated in 2022 or 2023, 31.2% of the patients developed grade ≥2 radiation dermatitis [12]. Moreover, several factors showed highly or almost highly significant associations with the occurrence of grade ≥2 dermatitis on multivariate analysis, including history of chronic inflammatory disease (*p*=0.001), history of significant cardiovascular disease (*p*<0.001), smoking history of more than 10 pack years (*p*<0.001), normo-fractionated radiotherapy (*p*<0.001), and administration of a radiation boost (*p*<0.001). These risk factors were considered when designing the current DAI-BREAC trial. This randomized trial compares the rate of grade ≥2 radiation dermatitis with standard skin care plus a reminder app to the dermatitis rate with standard skin care alone in a cohort of 268 patients. If it is demonstrated that the reminder app contributes to a clinically relevant reduction of radiation dermatitis in breast cancer patients, such an app will likely become a useful tool for this group in the near future. When the final results of the DAI-BREAC trial will be available, a limitation of this trial should be considered, namely the fact that standard skin care practices may vary between the contributing centers. This article considered the items recommended to address in the SPIRIT 2013 checklist [16–18].

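### Background skin care may vary by centre, but centre is not a stratification factor and the stated primary test is an unadjusted chi-square: no bias, but balance within centres is left to chance and some precision is given up

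*Protocol article*

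**What the plan says.** **Care and centres.** Under Standard skin care (Intervention description {11a}), both arms perform standard skin care four times a day, and "Standard skin care may vary at the participating centers". Only the regimen of one centre is described. Study setting {9} lists five sites: "Germany (one university hospital, two academic teaching hospitals, one private practice) and Denmark (one university hospital"). The Discussion comes back to the matter as "a limitation of this trial should be considered, namely the fact that standard skin care practices may vary between the contributing centers", and proposes no way of handling it.

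**Randomisation.** Sequence generation {16a} describes central 1:1 allocation in blocks of random size. The factors open with "Stratification will be done using the following prognostic factors:1.Treatment volume: Breast or chest wall alone vs. breast or chest wall plus lymph nodes2.Radiation boost", and the third is the presence of at least one risk factor for dermatitis. Two levels each give 2 × 2 × 2 = 8 strata. Centre is not a stratum, although the first digit of every patient number identifies it.

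**Analysis.** Sample size {14} states "A Chi-square Test will be applied". Statistical methods {20a} gives chi-square as the general method for two-by-two tables. It also names Cochran-Mantel-Haenszel (CMH) tests and logistic regression, but links neither to the primary endpoint or to any factor. It refers to an SAP to be finalised before database lock, which is not shown.

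**The concern.** The one source of heterogeneity that the authors themselves name is neither balanced by the design nor used in the stated primary comparison. If centres differ in background care, and so in their dermatitis rates, a chance excess of one arm in a high-rate centre moves the estimated app effect. The same holds for the three randomisation factors. The design goes to the trouble of balancing them, but a chi-square that ignores them still counts their variation as noise.

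At stake are precision, the credibility of the result when the conceded limitation is discussed, and freedom from a later choice between adjusted and unadjusted results once both are known.

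**Working it through.** **1. The plan's own figure.** Inputs from Sample size {14}: control rate 30%, app arm 15%, two-sided 5%, power 80%, 131 per arm, 2% not qualifying.
- The normal-approximation formula gives 121 per arm without and 134 with continuity correction.
- Exact power at 131 per arm is 80.1% for Fisher's test, 79.6% for the corrected chi-square and 83.7% for the uncorrected chi-square. So 131 is a Fisher-type or continuity-corrected size.
- 131/0.98 = 133.7, so 134 per arm and 268 in total, as stated. Nothing below changes these figures.

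**2. Balance within centres.** Recruitment {15} gives no split by centre. Assume equal centres: 268/5 = 53.6 patients each. With overall balance held but centre ignored, the SD of the arm difference in one centre is about √(53.6 × 0.8) = 6.5. Simulation (8 equal strata, blocks of 4 or 6, both assumed) also gives 6.5. The largest imbalance in any of the five centres is about 10 on average, with a 95th percentile of 17. With centre as an added stratum these become about 4.5 and 7, but in 40 cells of 268/40 = 6.7 patients.

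**3. What centre contributes to the error.** Assume centre rates of 20, 25, 30, 35 and 40%.
- Between-centre variance: (0.01 + 0.0025 + 0 + 0.0025 + 0.01)/5 = 0.005.
- Total binomial variance: 0.30 × 0.70 = 0.21. Centre share: 0.005/0.21 = 2.4%.
- SD of the arm difference: √(4 × 0.21/268) = 5.6 points. Centre part: √(4 × 0.005/268) = 0.86 points, already contained in the 5.6.
- For centre rates of 10 to 50% the variance is 0.02, the share 9.5% and the centre part √(4 × 0.02/268) = 1.7 points.

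**4. Error rate and power, centre only.** 4,000 simulated trials per row, N = 268, randomisation as planned, the app halving the rate. Monte Carlo error is about 0.35 points for type I error and 0.6 for power.

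| Centre rates (assumed) | Type I error, chi-square | Mean null difference | Power, chi-square | Power, CMH by centre |
|---|---|---|---|---|
| all 30% | 5.4% | −0.2 points | 84.8% | 84.3% |
| 20–40% | 4.9% | 0.0 | 85.1% | 85.4% |
| 10–50% | 4.9% | −0.1 | 83.9% | 85.6% |

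The gain from analysing by centre is about 0 to 2 points.

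**5. Randomisation factors.** Power ≈ Φ[(0.15 − 1.96·SE₀)/SE₁].
- With no prognostic effect, SE₀ = √(2 × 0.225 × 0.775/131) = 0.0516 and SE₁ = √((0.21 + 0.1275)/131) = 0.0508, giving 83.2%.
- Now let each of the three factors split patients evenly and shift the control rate by d (assumed). Between-stratum variance is V = 3(d/2)² in the control arm, V/4 in the app arm and 0.5625·V at the pooled rate.
- Stratified blocks lower SE₁ for both tests. Only a stratified test lowers SE₀ as well.
- Type I error of the unadjusted test is 2[1 − Φ(1.96·√(0.21/(0.21 − V)))].

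| d | V | Power, unadjusted | Power, stratified | Gain (points) | Type I error, unadjusted |
|---|---|---|---|---|---|
| 0.10 | 0.0075 | 83.6% | 84.2% | 0.6 | 4.6% |
| 0.15 | 0.0169 | 84.0% | 85.3% | 1.3 | 4.1% |
| 0.20 | 0.0300 | 84.6% | 87.0% | 2.4 | 3.4% |

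Simulations over a range of assumed heterogeneity put the gain at about 1 to 4 points and the unadjusted type I error at 3 to 5%.

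**6. Events available.** 131 × 0.30 + 131 × 0.15 = 39.3 + 19.7 = 59. Treatment, three factors and four centre terms make eight parameters: 59/8 = 7.4 events each.

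**The case against.** **No bias.** A reader might infer that differences in skin care are mixed into the app effect. They are not, in expectation: allocation is central, random and 1:1, so centre is independent of arm, and the simulated null difference is about zero even with centre rates of 10 to 50%. This stands in full.

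**Care is not on trial.** A reader might also take skin care as the treatment under test, or as shown to differ. The article says only that it may vary, and it is background care in both arms. The app is the tested difference. Local differences in grading are likewise an inference: the article prescribes one scale (CTCAE v5.0) and experienced observers.

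**The effect is small.** Under the 20 to 40% spread the centre part is 0.86 points inside a sampling SD of 5.6, and even 10 to 50% yields under two power points. This stands, and it limits the point to an improvement.

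**Leaving centre out of the strata is defensible.** Forty cells of 6.7 patients would be thin, and the Discussion ties the design to risk factors found in the group's earlier study. This stands, so the randomisation should not be changed.

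**Covariates belong in the SAP.** This stands in part. An unnamed centre term is not an omission as such, and it cannot be inferred that the SAP lacks one. But the article does fix a test for the primary comparison, and that test is unadjusted. The adjusted methods it names are attached to nothing.

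**Conclusion.** The point holds as a modest one about efficiency and pre-specification. Background care may vary across five centres, centre is not a stratum, and the stated chi-square uses neither centre nor the three factors on which patients are randomised. The type I error is not inflated; ignoring the randomisation factors makes the test slightly conservative if anything.

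The cost is chance imbalance within centres (largest typically about 10 of about 54 patients) and lost power of about 0 to 2 points for centre and about 1 to 4 for the randomisation factors. The sample size is unaffected.

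The sizes rest on assumptions not in the documents: equal centres, equal strata, blocks of 4 or 6, and the stated spreads of rates. Unequal centres would change the imbalance figures but not the absence of bias.

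**What to change.** Leave the running randomisation as it is. Before database lock, state that:

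- the primary comparison is adjusted for treatment volume, boost, risk factor and centre, using a method already named in Statistical methods {20a};
- small centres are pooled by a rule fixed in advance;
- the adjusted risk difference is reported beside the unadjusted chi-square, and it is fixed beforehand that the adjusted comparison is primary;
- the arm difference is shown by centre, descriptively only.

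Logistic regression with the treatment effect standardised to a risk difference suits this best. Without standardisation the result is a conditional odds ratio, which is not the difference in rates on which the trial was sized. CMH over all four factors would have 40 cells with about 59/40 = 1.5 events each.

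The cost is SAP wording, since centre is already recorded; up to seven covariate terms on about 59 expected events, about seven events per parameter; and the pooling rule. The departure from the chi-square used for sizing should be stated openly.

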### Concealment mechanism {16b}

Allocation of a patient to a treatment arm will be performed using an eCRF.

### Implementation {16c}

Generation of the allocation sequence, enrollment of participants and assignment of participants to interventions will be performed by specially trained physicians registered as investigators for this trial.

## Assignment of interventions: Blinding

### Who will be blinded {17a}

Data analysts and statisticians will be blinded. Moreover, the person assessing radiation dermatitis will be different from the person who performs the routine visit of the patient (“blinded observer concept”),

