### Trial design {8}

This is a multinational, randomized, active-controlled, open-label, multicenter, parallel-group trial, which compares the following treatments of radiation related skin toxicity in patients with breast cancer:

Standard skin care supported by a reminder app (Arm A) vs. standard skin care alone (Arm B).

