### Eligibility criteria {10}

Inclusion criteria1.Histologically proven invasive breast cancer2.Indication for adjuvant hypo-fractionated radiotherapy [8, 9]3.Possession of and ability to use a smartphone4.Female gender5. Age ≥18 years6.Written informed consent7.Capacity of the patient to consent

Exclusion criteria1.Pregnancy, Lactation2.Expected non-compliance

Male patients were not included, since male breast cancer is increasingly considered a separate tumor entity with a biological behavior different from female breast cancer [10]. Radiation dermatitis will be assessed by an experienced observer (specially trained nurse, technician, or physician) different from the person who performs the routine visit of the patient (“blinded observer concept”), at the start of radiotherapy, weekly during the course of radiotherapy, and at the end of radiotherapy.

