### Strategies to improve adherence to interventions {11c}

Patients will be seen by staff members (radiotherapy technologists) of the treating Department of Radiation Oncology during each treatment session and additionally by investigators of the trial once a week.

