### Procedure for unblinding if needed {17b}

Each investigator trained for the trial and listed in the delegation log has an individual password protected access to the eCRF, where the information regarding the patient’s allocation is available.

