### Data collection and management

#### Plans for assessment and collection of outcomes {18a}

The following parameters will be recorded at the start of the trial: medical history including concomitant diseases (particularly chronic inflammatory disease, cardiovascular disease, and smoking habits), medication including systemic anticancer treatment, physical examination, age, date of birth, gender, body height and body weight, performance status (ECOG-PS [13]), tumor side (affected breast) and location, stage, histology, hormone receptor status, HER2 status, Ki-67 labeling index, triple-negativity, planned total radiation dose, dose per fraction, number of fractions, radiation boost, treatment volume (breast alone, chest wall alone, breast plus lymph nodes, chest wall plus lymph nodes), radiation technique, deep-inspiration breath hold (DIBH) technique, and pain score including the intake of analgesics.

The following parameters will be assessed during the course of the trial:1. Radiation dermatitis: Assessed by an observer different from the person who performs the routine visit of the patient at the start of, weekly during, and at the end of radiotherapy (CTCAE v5.0) [11] .2. Pain (skin within radiation fields): Assessed prior to, weekly during, and at the end of radiotherapy (visual analogue scale). Furthermore, intake of analgesics will be documented.3. Adverse events other than radiation dermatitis will be assessed on an ongoing basis (CTCAE v5.0) [11].4. Eastern Cooperative Oncology Group (ECOG): Evaluated prior to and at the end of radiotherapy [13].5. Physical examination: Performed prior to, weekly during radiotherapy, and at the end of radiotherapy.6. Patient satisfaction with the reminder app, its impact on the use of health technology, and benefit from support (coaching) by staff members: Assessed with specific questionnaires at the end of radiotherapy.

The timeline of trial procedures and assessments is given in Figure 1.

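### Blind assessment of the primary endpoint is labelled but not secured: the dermatitis assessor has only to be a different person, not unaware of the arm

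*Protocol article*

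**What the plan says.** The section Trial design {8} is plain about the setting: "This is a multinational, randomized, active-controlled, open-label, multicenter, parallel-group trial". The primary endpoint (Outcomes {12}) is the rate of grade ≥2 radiation dermatitis by CTCAE v5.0 at the end of radiotherapy.

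The assessor is described in three places:

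- Eligibility criteria {10}: an "experienced observer (specially trained nurse, technician, or physician) different from the person who performs the routine visit of the patient", given the label of a blinded observer.
- Who will be blinded {17a}: "Data analysts and statisticians will be blinded", followed by "the person assessing radiation dermatitis will be different from the person who performs the routine visit of the patient", with the same label.
- Plans for assessment and collection of outcomes {18a}: "Assessed by an observer different from the person who performs the routine visit of the patient", without the label.

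Procedure for unblinding if needed {17b} says that each trained investigator on the delegation log "has an individual password protected access to the eCRF, where the information regarding the patient’s allocation is available". It names no condition of need and no limit by role. Under Data management {19}, trial data are collected in eCRFs.

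**The concern.** Separating the assessor from the routine visit gives independence from the treating contact. It does not give masking. A site could follow all three descriptions to the letter while the assessor knows the arm.

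Patients cannot be masked to a phone app, so masking the assessor is the main protection against detection bias. The endpoint is a yes/no cut between grade 1 and grade 2 made by an observer, and an arm-aware assessor could move borderline cases across it without intending to. Grading is repeated weekly and at the end of radiotherapy, so patients have several chances to mention the app.

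The cost would be to credibility. A positive result reported as blindly assessed would claim more protection than the protocol requires, and a critic could not be answered from the text.

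**Working it through.** **1. What the text secures.**

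| Question | Answer in the protocol article |
|---|---|
| Is the assessor separate from the routine visitor? | Yes, in {10}, {17a} and {18a} |
| Must the assessor be unaware of the arm? | Not stated in any of the three |
| Who may assess? | Trained nurse, technician or physician ({10}) |
| Who can see the allocation in the eCRF? | Every trained investigator on the delegation log ({17b}) |
| Who are the investigators? | Specially trained physicians registered as such ({26a}, {16c}) |
| May the assessor also coach the patient on the app? | Neither allowed nor barred |

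The eCRF point therefore applies to physician-investigators who act as assessors. It does not clearly extend to nurses or technicians.

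**2. The sample size used below.** Sample size {14} gives 131 per arm in the Full Analysis Set, from 30% against 15%, two-sided 5% and 80% power. At 131 per arm, exact enumeration of Fisher's test gives 80.1% power, and the continuity-corrected formula gives 134 per arm (the uncorrected formula gives 121). Allowing for 2% loss, 131/0.98 = 133.7, so 134 per arm and 268 in total, as stated. The 131 is taken as given.

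**3. Illustration of what is at stake.** The document gives no misgrading rate, so the share m is an assumption and is shown over a range. The true rate p is the same in both arms: 25.4% (the retrospective rate) or 30% (the planning rate), both from {14}.

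- One direction: a share m of Arm A cases is graded down. Observed rates are p(1 − m) in Arm A and p in Arm B, a difference of pm.
- Both directions: in addition, a share m of Arm B non-cases is graded up. Arm B becomes p + m(1 − p), and the difference is p + m(1 − p) − p(1 − m) = m.

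Worked case, p = 0.254, m = 0.10, both directions:

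- Arm A: 0.254 × 0.90 = 0.2286. Arm B: 0.254 + 0.10 × 0.746 = 0.3286. Difference 0.1000; mean rate 0.2786.
- Standard error under the null: √(2 × 0.2786 × 0.7214/131) = 0.0554.
- Standard error under the observed rates: √((0.2286 × 0.7714 + 0.3286 × 0.6714)/131) = 0.0550.
- Probability of significance: Φ((0.1000 − 1.96 × 0.0554)/0.0550) = Φ(−0.156) ≈ 0.438. Exact binomial enumeration gives 43.9%.

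Exact enumeration, uncorrected chi-square test, two-sided 5%, 131 per arm:

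| Assumed misgrading | p = 25.4%: difference, significant | p = 30%: difference, significant |
|---|---|---|
| None | 0 points, 5.0% | 0 points, 5.0% |
| 10%, Arm A down only | 2.5 points, 7.7% | 3.0 points, 8.4% |
| 20%, Arm A down only | 5.1 points, 16.5% | 6.0 points, 19.4% |
| 5%, both directions | 5 points, 14.9% | 5 points, 14.2% |
| 10%, both directions | 10 points, 43.9% | 10 points, 41.3% |

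In the 10% two-directional case at 25.4%, about 7.5 of the 10 points (0.10 × 74.6%) come from grading up Arm B non-cases and about 2.5 (0.10 × 25.4%) from grading down Arm A cases. That scenario depends mostly on the up-grading assumption.

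**The case against.** The design is openly declared open-label, the scale is a standard one, the observers are trained, and they are separated from the routine visit. One could add that eCRF roles, delegation rules and patient instructions usually sit in the full protocol or site procedures, which are not shown. Section {17a} also ends on a comma and may be cut short.

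Part of this stands. Missing operational detail is not the fault here. The fault is that the article defines its own safeguard, and the definition does not deliver what the label says. The sentence in {10} is complete and carries the same rule, so the comma does not rescue it.

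Four stronger readings are tempting, and the document does not support them:

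- *The endpoint is in fact graded with knowledge of the arm.* No section says so.
- *All assessors can look up the allocation.* Section {17b} speaks of investigators, who are physicians elsewhere in the article. Access for nurse or technician observers is not described.
- *Daily contact with technologists, or coaching, unmasks the grader.* Technologists see patients of both arms at every session, and seeing a patient does not reveal a phone app. Coaching of Arm A patients is mentioned, but nothing says that coaches grade dermatitis.
- *Analyst blinding fails because the app questionnaires exist only in Arm A.* That depends on when these data are released to the analysts, which is a matter for the analysis plan and is not shown.

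**Conclusion.** The point holds in a limited form. The article claims a blinded observer for the primary endpoint but requires only a different person, and it leaves the allocation open in the eCRF to any physician-investigator who assesses. Blind grading is possible under this text but not secured by it.

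The bias, if any, has no size that the document can supply. Under the assumptions above, one-directional misgrading of 10% does modest harm (about 8% false significance against a nominal 5%). Misgrading of 10% in both directions would be serious (about 41% to 44%). These figures show sensitivity to the safeguard and are not estimates of what will happen.

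This should be corrected because it concerns the primary endpoint and is easy to settle. It is an ambiguity that clear wording can close, not a flaw that invalidates the trial.

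**What to change.** - In {10}, {17a} and {18a}, state that the dermatitis assessor must be masked to allocation.
- In {17b}, state that assessors do not use an eCRF view that shows the allocation or the Arm A forms.
- State that the person who coaches a patient on the app does not grade that patient.
- Ask patients not to mention the app to the assessor, and record when an assessor becomes unmasked.
- Where a site cannot comply, drop the word blinded and report the endpoint as graded by an independent but unmasked observer, with this listed as a limitation.

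The cost is a few sentences, an eCRF role setting and a site instruction. A separate assessor is already planned. The downside is that delegation must keep coach and grader apart, which may be harder at the private practice site. Recruitment was planned to run for 24 months from December 2024, so the change protects only patients not yet graded. Earlier gradings should be described by the rule in force when they were made.
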